## Results

The EatSmart website has been developed, tailored to the needs of people of lower SEP with T2D, and all the modules viewed by participants. Recruitment began in October 2019 and finished in February 2020. Data collection will continue through October 2020. Data analysis and cleaning will be conducted after data collection is complete. We anticipate reporting results in December 2020 by submitting professional publications in peer-reviewed journals and conference presentations.

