**Methods:**

EatSmart is a mixed methods (quantitative and qualitative) pre-post design pilot study. Sixty socioeconomically disadvantaged people with T2D aged 18 to 75 years will be recruited. Participants will complete self-reported baseline assessments of their basic demographic and clinical data, dietary intake, dietary self-efficacy, and barriers to healthy eating. They will be provided with login access to the EatSmart web program, which includes six progressive skill-based modules covering healthy eating planning; smart food budgeting and shopping; time-saving meal strategies, healthy cooking methods, modifying recipes; and a final reinforcement and summary module. Over the 3-month intervention, participants will also receive 3 text messages weekly, encouraging them to review goals, continue to engage with different components of the EatSmart web program, and eat healthily. Participants will undertake follow-up assessments directly following the intervention 3 months post baseline and again after a 6-month postintervention follow-up period (9 months post baseline). Feasibility will be evaluated using the number of participants recruited and retained and objective indicators of engagement with the website. Program appeal and potential effects on primary and secondary outcomes will be assessed via the same surveys used at baseline, with additional questions asking about experience with and perceptions of the program. In-depth qualitative interviews will also be conducted 6 months post intervention to provide deeper insight into experiences with EatSmart and a more comprehensive description of the program’s appeal.

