As part of EatSmart, participants receive three unidirectional text messages/week (36 in total), at a time they indicate is convenient, to encourage them to maintain healthy eating, review their goals, and continue to engage with different components of the website (Multimedia Appendix 4). Multiple behavioral change techniques, including goal setting on core food group intake, informing about health and social (cost) consequences, instructions on how to perform behaviors, and self-monitoring behavior, were employed to design the text messages.

After consenting to the study, participants complete baseline assessments immediately in person or at a more convenient time by telephone or through a secure weblink. The baseline evaluation requests information on basic demographic and clinical data, dietary intake, dietary self-efficacy, and barriers to healthy eating. Upon completing baseline assessments, participants are shown how to log on to the website using their username and password. Once logged in, participants can access the six intervention modules offered to them consecutively on a biweekly basis. Each module can be completed in around 15 minutes, but no recommendation or limitation regarding timing and usage will be given. Therefore, they can read the materials and engage with the website in a suitable and convenient timeframe.

Following intervention completion at three months, participants undertake the same baseline evaluation (except for demographic details). During the 6-month follow-up period (3 to 9 months post baseline), participants will have free access to all website materials; however, they will not receive text messages. After the 3-month data collection period, all participants who complete the postintervention assessments (regardless of their level of engagement) will receive an AU $50 (US $35) shopping voucher as compensation for their time. Those who complete the online follow-up survey will receive an AU $20 (US $14) shopping voucher, and those who agree to be interviewed will receive an extra AU $20 (US $14) shopping voucher.

**Table 1 table1:** Summary of intervention components, targeted determinants, and behavior change techniques.

Intervention component	Primary message/resources (web + text message)	Targeted determinant	Behavior change techniques

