### Outcomes and Measures

This study’s primary outcome is pre-post intervention (baseline versus 3 months) changes in the consumption of vegetables and fruits.

Secondary outcomes are:

Six-month follow-up changes in consumption of vegetables and fruits (baseline versus 9-month),Pre-post intervention and 6-month follow-up changes in other dietary indicators aligned with dietary guidelines (wholemeal/whole grain bread, milk, water, and some discretionary items),Pre-post intervention and 6-month follow-up changes in dietary self-efficacy (including perceived skills and confidence),Pre-post intervention and 6-month follow-up changes in perceived barriers to healthy eating (including budget/perceived unaffordability, family preferences, taste, and skills),Feasibility and engagement,Appeal, satisfaction, usability, and longer term acceptability of the program.

Study measures across time points are presented in Multimedia Appendix 5. Demographic data including age, sex, education level, country of birth, and family/household composition will be gathered using a standard survey. Clinical data, including the duration of diabetes and current diabetes medications, will also be collected to describe the sample. Dietary intake will be assessed by a survey with short dietary intake questions. The survey includes five multiple-choice questions regarding the consumption of vegetables and fruits and 12 questions asking about the consumption of wholemeal/whole grain bread, milk, water, and some discretionary items. The single fruit and vegetable questions are adapted from those used in Australia’s National Nutrition Survey (1995), which were shown to discriminate between groups with different vegetable intakes assessed by a 24-h recall. The self-report Food Frequency questions are based on those used in the ShopSmart study [58]. Additional questions regarding the consumption of starchy vegetables and legumes were also designed and added to the survey to capture important outcomes for this T2D target group. Dietary self-efficacy and barriers as key predictors of dietary changes will be assessed by established self-report survey items, including 27 statements with Likert scale responses [59,60].

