Feasibility and engagement will be evaluated by the number of participants recruited/retained, numbers accessing the website, logins and duration of website use, pages engaged with, and numbers receiving/reading the text messages [61]. For this purpose, web tagging is applied to the EatSmart website to record usage systematically. Tagging logs user interaction with particular program features and can provide real-time and historical statistics on engagement [62]. Website analytics allow us to identify whether portal login and usage are continuous, declining, or fluctuating during the intervention and follow-up period. In this intervention, we will consider adherence to the program to be confirmed by at least 66% of participants completing the study. We will also assess the number of website modules visited, as well as text messages read. While there is no set definition of feasibility in the literature for this context, we would consider the approach feasible if participants engage with the majority of materials (ie, on average more than 50% of website pages and text messages). However, we will also explore reasons for lower engagement levels through our semistructured interview to improve the materials for future larger studies. Program appeal, usability, and participants’ satisfaction will be assessed by self-report survey questions developed for this study. These include three statements with Likert scale responses and 11 open-ended qualitative questions about using the educational materials, useful features of the website and the messages, and liked and disliked aspects of the EatSmart program.

Participants will complete all self-report surveys, either web-based or telephone-assisted, at baseline and again at 3 and 9 months. The data capture and management tool REDCap (Research Electronic Data Capture) [63] will be used to collect data. Data will be entered automatically by the participant, via an individualized hyperlink or manually (by the research fellow), into REDCap. The data is stored, housed, and backed up within Deakin University in a database that can only be accessed via three layers of security (university firewalls, institute limitations, and project manager login).

Data on program appeal, usability, and participant satisfaction will be supplemented by semistructured interviews at 6 months post intervention to explore longer term maintenance of any behavioral or attitudinal changes.

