At 9 months post baseline, participants will be invited by telephone, text message, or email to complete a one-on-one semistructured interview of up to 40 minutes via telephone. Recruitment for interviews will be successive until no new themes appear (thematic saturation). However, based on other qualitative reports in the same area [64-66], we do not expect to recruit fewer than 25 participants. Interview methods are useful for gaining specific information while allowing participants to freely share their viewpoints [62]. These interviews will be conducted to understand participants’ experiences of the EatSmart program and answer questions about whether, how, and why the intervention modules created long-lasting behavioral changes. The researcher will use a discussion guide of open-ended questions, and the interview will be audio recorded to ensure all verbal data are captured. The researcher will also write notes after the interview to document related nonverbal data. Participants will answer questions about the various parts of the website, text messages, and content presented within the intervention, their perceived capability for action within their personal situation, and any subsequent healthy eating-related changes.

These interviews will add to the program feedback from the surveys and create a base for understanding the characteristics of patients for whom these healthy changes occur and last. These data will provide us with insight into contextual factors that promote engagement.

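### Data collection is stated to end in October 2020, but participants with a February 2020 baseline reach the 9-month survey and interview in November 2020

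*Protocol article*

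**What the plan says.** The Results section of the protocol article gives the calendar: "Recruitment began in October 2019 and finished in February 2020. Data collection will continue through October 2020". It adds that cleaning and analysis follow the end of collection and that results are expected to be reported in December 2020.

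The length of follow-up is stated several times and consistently. The Abstract places the last assessment "again after a 6-month postintervention follow-up period (9 months post baseline"). Under Intervention, the post-intervention follow-up runs from month 3 to month 9. Under Outcomes and Measures, the surveys are completed "at baseline and again at 3 and 9 months", and one secondary outcome is "Six-month follow-up changes in consumption of vegetables and fruits (baseline versus 9-month"). The qualitative component uses the same time point: "At 9 months post baseline, participants will be invited by telephone, text message, or email to complete a one-on-one semistructured interview".

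The Intervention section also allows the baseline survey to be done at consent or later, by telephone or weblink. The article states no window for the 9-month assessment and no shorter follow-up for late recruits.

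**The concern.** The last recruitment month, the follow-up length and the end of data collection cannot all be right. February plus nine months is November, so the stated end comes before the last participants are due.

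The 9-month time point carries the follow-up comparisons for vegetables and fruits, the other dietary items, self-efficacy and perceived barriers. It also carries the interviews meant to show whether any changes last. If the October date were applied, late recruits would either be missing from these analyses for an administrative reason or be measured early under a 9-month label. The December 2020 reporting date adds pressure: it leaves little time after a November close and could encourage cutting off the last recruits.

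**Working it through.** **Inputs, all from the protocol article**
- Recruitment: October 2019 to February 2020, so the last possible recruitment date is 29 February 2020 (Results).
- End of data collection: October 2020, read as generously as possible as 31 October 2020 (Results).
- Final assessment: 9 months after baseline (Abstract; Intervention; Outcomes and Measures).
- Intervention length: 12 weeks, also described as 3 months (Intervention), which permits a slightly shorter clock.
- Baseline is at consent or later (Intervention). It is taken here as the recruitment date, the earliest possible.

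**Can the stated end date be reproduced?**

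Due date = baseline date + 9 months.
- 1 February 2020 + 9 months = 1 November 2020.
- 29 February 2020 + 9 months = 29 November 2020.
- Working back, 31 October 2020 − 9 months = 31 January 2020, the last baseline date that fits.

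October 2020 is therefore not reproduced. The shortfall is 1 to 29 days, and longer where the baseline survey was delayed after consent.

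**Does a shorter reading of 9 months remove the conflict?**

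| Clock | Last baseline due by 31 Oct 2020 | February dates due later | Due date for a 29 Feb baseline |
|---|---|---|---|
| 9 calendar months | 31 Jan | 29 of 29 | 29 Nov |
| 39 weeks | 1 Feb | 28 of 29 | 28 Nov |
| 12 weeks + 6 months | 6 Feb | 23 of 29 | 23 Nov |
| 12 + 26 = 38 weeks | 8 Feb | 21 of 29 | 21 Nov |
| 9 × 4 = 36 weeks | 22 Feb | 7 of 29 | 7 Nov |

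No version accommodates recruitment to the end of February. These are counts of calendar dates, not of participants.

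**Primary outcome**

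29 February 2020 + 3 months = 29 May 2020, well inside the stated period. The baseline-to-3-month comparison is not touched.

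**The case against.** The strongest reply is that the sentence in Results is a progress forecast in a journal article, not a cut-off rule. Nothing in the article says that surveys are refused after 31 October or that late recruits are truncated. The design rule, stated consistently, is 9 months after baseline. This stands in part: the article does not show that anyone will be lost. It does print a date that its own design contradicts, and it makes analysis wait for that date.

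A second reply is that recruitment may have finished early in February. On a clock of 12 weeks plus 6 months, baselines up to 6 February fit, so the loss could be nil. This also stands as a limit. A reader might infer that every February recruit falls outside October, but that holds only for 9 calendar months, and neither the closing day nor the February count is given.

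A third reply is that the damage is limited. The primary outcome is at 3 months, all effects are declared exploratory, the planned mixed models can still use late recruits' baseline and 3-month data, and interviews are recruited to saturation rather than from all 60 participants. All of this is correct. It reduces the weight of the point but does not reconcile the dates.

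A reader might go further and infer that the cut-off would cause the study to miss its criterion of at least 66% of participants completing. The documents do not support that, for three reasons:
- The criterion is not tied to a time point. If it means the 3-month programme, it is unaffected.
- A projected loss needs a February share, which is not reported. Even recruitment over the 152 days from 1 October to 29 February would give 29/152 = 19%, but nothing in the article says that recruitment was even.
- The 33% drop-out figure under Sample Size Estimation is an upper limit, so it cannot be added to such a loss as though it were the expected rate.

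Nor does the article say that participants who are not yet due would be counted as drop-outs.

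**Conclusion.** The point holds as a date inconsistency with a confined consequence. With recruitment ending in February 2020 and a final assessment at 9 months, October 2020 is too early by up to 29 days on calendar months if baseline coincided with recruitment, and by more if baseline came later. On 12 weeks plus 6 months, baselines after about 6 February remain outside.

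If collection did close in October, the participants concerned would lack the 9-month secondary outcomes and the interview, or would be measured up to about a month early. How many of the 60 this is cannot be determined from the article. The 3-month primary outcome is not affected, and no conclusion about the completion criterion follows.

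The verdict assumes that the recruitment dates and the 9-month schedule are stated correctly and that no assessment window is defined elsewhere that would cover the gap.

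**What to change.** - Replace the October 2020 end date with the date on which the last participant completes the 9-month survey and interview. If recruitment ran to the end of February, this is at least the end of November 2020, and later where baseline was completed after consent.
- Start cleaning and analysis of the 9-month data only after that date.
- Move the December 2020 reporting date for the 9-month results if needed.
- State that participants who have not yet reached 9 months are not counted as non-completers.

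The cost is one or two sentences and about one more month of web or telephone surveys and interviews. The downside is that the 9-month report comes slightly later.

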## Discussion

As with many chronic diseases, a disproportionately high burden of diabetes and its associated complications is shouldered by those who are socioeconomically disadvantaged. This target group is often neglected in research trials as they are generally considered too hard to reach and impact [71]. EatSmart is one of the first international studies to deliver theoretically grounded, evidence-based support digitally to enable disadvantaged people with T2D to strengthen skills necessary to eat healthily on a budget, as a key part of diabetes self-management. EatSmart offers a potentially low-cost approach with high reach, with the only cost to participants involving minimal data use to access the website from their existing internet service.

Several approaches have been employed to increase the efficacy of EatSmart. Firstly, in all stages of the website’s design, development, and content, the end users’ particular needs and perspectives have been evaluated and considered. Secondly, a behavioral support reminder system in the form of regular text messages helps promote continued engagement and address the problem of high attrition rates, a problem common to eHealth studies [72]. Furthermore, the intervention framework is theoretically grounded in Bandura’s Social Cognitive Theory [47], emphasizing the importance of factors within the cognitive, socioenvironmental, and behavioral domains and their interactions. Key constructs of Social Cognitive Theory are goals (plans to act that can be deemed as intentions to perform the behavior), self-efficacy (peoples’ judgment of their ability to perform a behavior), and outcome expectations (views about the outcomes that are possible to result from a specific behavior).

EatSmart targets nutritional knowledge gaps and misinformation, promotes positive mindsets toward healthy eating (ie, self-efficacy), and facilitates changes in eating behaviors to increase self-efficacy and behavior change. Active learning, guided practice, reinforcement, and modeling are key features of Social Cognitive Theory contained within EatSmart. Some of the strategies incorporated into the design of EatSmart included goal setting and problem solving for building self-management skills, providing hands-on skill-building activities (eg, cooking activities utilizing healthy ingredients and cooking methods), and direct instruction and modeling by the intervention nutritionist (in videos). Modeling is an important influence, providing individuals with skills and strategies to adopt and maintain behaviors in different situations. The video components of the EatSmart website incorporate modeling, with actors (research team members) providing support in real-world environments such as the supermarket and the kitchen at home. The intervention also draws on empirical evidence of the key determinants of eating behaviors, including our past work suggesting the significance of addressing nutrition knowledge, food planning and budgeting and preparation skills, perceived and actual food costs, and other barriers [11]. Finally, the mixed methods design and the inclusion of in-depth qualitative interviews can provide deep insight into the challenges and promises of employing eHealth healthy eating interventions for disadvantaged people with T2D.

The results of this pilot study will be interpreted with consideration of the following limitations. The study relies on self-reported measures, which may be subject to recall and social desirability bias. The lack of a control group is another limitation, although this is an appropriate design for a pilot study in a relatively new area, with feasibility and exploratory focus. Furthermore, while clinicians and 12 randomly selected patients with T2D were involved in reviewing and providing input to a draft website, there could have been greater involvement from these groups throughout the development of the intervention. However, as it is a pilot study, the feedback survey and interviews will be used to further inform the development of future interventions. Finally, EatSmart is currently only presented in English, which is essential to evaluate the feasibility of this initial pilot trial. Translation to other languages can be a future priority to reach other underserved communities at higher risk of health disparities.

The EatSmart intervention study results will make a valuable contribution to the evidence base on diabetes self-management in a high-risk population. This project will inform scalable public health programs to promote healthy eating and diabetes self-management as an inexpensive adjunct to clinical care among vulnerable populations and contribute new knowledge to digitally delivered health research in Australia and internationally.

## Appendix

Multimedia Appendix 1 Participant Information and Consent Form.

Multimedia Appendix 2 Participant Information and Consent Form (Follow up interview).

Multimedia Appendix 3 HCP Information and Consent Form.

Multimedia Appendix 4 Text messages provided in the EatSmart program.

Multimedia Appendix 5 Study measures and assessment tools across time points.

## Abbreviations

SEP: socioeconomic position
T2D: type 2 diabetes
